## Abstract

**Background:**

Activity advice and prescription are commonly used in the management of low back pain (LBP). Although there is evidence for advising patients with LBP to remain active, facilitating both recovery and return to work, to date no research has assessed whether objective measurements of free living physical activity (PA) can predict outcome, recovery and course of LBP.

**Methods:**

An observational longitudinal study will investigate PA levels in a cohort of community-dwelling working age adults with acute and sub-acute LBP. Each participant's PA level, functional status, mood, fear avoidance behaviours, and levels of pain, psychological distress and occupational activity will be measured on three occasions during for 1 week periods at baseline, 3 months, and 1 year. Physical activity levels will be measured by self report, RT3 triaxial accelerometer, and activity recall questionnaires. The primary outcome measure of functional recovery will be the Roland Morris Disability Questionnaire (RMDQ). Free living PA levels and changes in functional status will be quantified in order to look at predictive relationships between levels and changes in free living PA and functional recovery in a LBP population.

**Discussion:**

This research will investigate levels and changes in activity levels of an acute LBP cohort and the predictive relationship to LBP recovery. The results will assess whether occupational, psychological and behavioural factors affect the relationship between free living PA and LBP recovery. Results from this research will help to determine the strength of evidence supporting international guidelines that recommend restoration of normal activity in managing LBP.

**Trial registration:**

[Clinical Trial Registration Number, ACTRN12609000282280]

## Background

Low back pain (LBP) is a common [1] costly [2] and at times disabling condition [3] with a high prevalence across a range of occupational settings [4-7]. Although LBP mostly settles within 3-4 weeks [8] of onset, a significant proportion will either not resolve or will recur [9]. The direct and indirect healthcare costs associated with chronic LBP and resultant disability and work absence are considerable [10]. In an attempt to reduce costs and facilitate return to work, national and international LBP guidelines [11,12] recommend restoration of normal activity as an integral part of the management of acute and sub-acute back pain, and occupational health guidelines recommend and encourage an early return to work [13]. Advice to stay active as an adjunct to exercise produced more favourable results then exercise alone when included in standard care for patients with acute LBP [14] and there is strong evidence for supporting early mobilisation and activity in the treatment of acute LBP [15,16].

Currently there is limited evidence for physical activity (PA) facilitating prognosis of occupational LBP [17-19]. One study found that regular exercise outside of work tended to protect against recurrence of work-related LBP [19], and another that leisure time PA levels were predictive of return to work in patients who had undergone a light mobilization program after initial LBP sick leave [17]. Storheim [18] also found a significant positive relationship between higher fitness levels and return to work in patients with chronic LBP. A number of studies have explored relationships between PA and risk of developing occupational LBP [20-22], or looked for relationships between pre-injury activity and LBP outcome [23]. A recent systematic review did not identify activity level as a predictor for return to work in patients with acute LBP [24], however none of the included studies objectively and prospectively measured PA, and its relationship to outcome.

Cross sectional studies provide little evidence for a direct link between PA and LBP outcomes [25-27] and prospective cohort studies investigating the potential relationships between PA levels and LBP show mixed results [28-31]. Bousema [29] employed an accelerometer to measure PA at two time points over a 1 year period and reported no difference in PA level changes between groups classified as "recovered LBP" and "non-recovered LBP". Similarly, Leonhardt [30], using an activity recall questionnaire, found that development of chronic pain had no influence on the total energy expenditure at six months in a mixed cohort of patients with acute and chronic LBP. Hurwitz [28] reported that both the cross sectional and longitudinal odds ratio for back disability were significantly reduced in those who had the greatest levels of leisure time PA levels. However, Mortimer [31] found that non-specific regular exercise (measured with a recall questionnaire) did not seem to improve LBP outcomes at 5 year follow-up. Thus evidence for a relationship between PA levels in free living and functional recovery in patients with LBP appears to be equivocal.

Research priorities in LBP and the prevention of work-related musculoskeletal disorders recommend prospective studies to monitor and assess the natural course of LBP over time, and in particular to look at factors that are predictors for chronicity and search for effective preventive measures [32,33]. Dose response relationships between activity levels, including types, frequencies and duration should also be explored using validated functional outcome measures [34,35].

Accurate assessment of the amount and intensity of PA in daily life is considered important due to the strong relationship between PA levels, health and disability [36,37]. However, it is recognised that the measurement and capture of the various dimensions of PA in free living is problematic [38]. Variance and fluctuations within normal free living activity levels, [39,40] and debate regarding measurement tools and time required to accurately portray and reliably measure free living PA, [41,42] mean that there is a lack of consensus on an optimal approach to measure free living activity. However, recommendations suggest a repeated measures (longitudinal) design that includes an objective measure of PA [43,44] will likely provide the most accurate method of estimating PA in free living [45]. To date no studies have prospectively employed an objective measure of PA to investigate the predictive relationship between PA in free living and a validated LBP outcome in a cohort of patients with acute LBP.

Accelerometers provide an objective tool for the assessment of PA in free living populations over periods long enough to be representative for normal daily life [44]. Triaxial accelerometers have been used to measure and quantify PA within several patient populations [46-48]. The RT3 triaxial accelerometer provides a valid and reliable measure of PA [49-51] and has been previously utilised as a measure of PA change within defined patient populations [52,53].

## Methods

### Research objectives

1. To investigate the predictive relationship between change in objectively measured PA levels in a cohort of patients with acute (< 6 weeks' duration) LBP [54] from baseline to 3 months, and change in functional outcome at 3 months and recovery over a 1 year period.

2. To assess the effect of occupation and occupational activity levels, personal factors, pain levels, functional status and psychosocial profile on the relationship between PA levels and LBP outcomes at 3 months and at 1 year.

3. To determine the relationship between restoration of "normal" levels of PA as considered by the patient and functional recovery.

### Hypotheses

Three specific hypotheses will be tested:

1. Positive changes in PA levels of participants with acute LBP (from baseline to 3 months) are a positive predictor of recovery (defined from change score in *Roland Morris Disability Questionnaire*) [54] at 3 months and at 1 year;

2. Psychosocial factors including levels of fear avoidance beliefs, depression and anxiety and occupational factors including types of occupation and levels of manual or sedentary work act as confounders in the relationship between activity change and the course of LBP over a 1 year period;

3. Restoration of "normal" levels of PA at baseline and at 3 months is a positive predictor of functional recovery over a 1 year period.

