### Physical activity measurement

All RT3 monitors will undergo testing prior to field use as part of the standardised protocol recommended when employing accelerometry measurement [69,70]. Previous research has shown high levels intra-monitor variability [49] and therefore each participant will be required to use the same RT3 monitor at baseline and 3 months. Field practice of monitor use and monitor placement will be standardised by asking the participants to wear the RT3 monitor on the right hip for all waking hours; to report wear times and reason for removal; to note the days that they work; and also to report sleep patterns [70] and hourly activities in an activity diary over the week [53].

The dimensions and specifics of the RT3 have been reported previously [49]. The RT3 triaxial accelerometer stores accumulated activity counts, derived from the three axes ([X^2 ^+ Y^2 ^+ Z^2^]^0.5^) to calculate a summed VM. Mode 4 will be employed for this study, which stores accumulated activity counts every second and calculates an average VM for each one-minute epoch over the 7 days of monitoring. Previous research has validated the use of RT3 VM counts as a measure of free living activity and energy expenditure [50].

Participants will be contacted twice during this week by text and/or phone to improve compliance in wearing the RT3, recording activity in the activity dairy, and to address any problems the participants might be having with either the RT3 or in using the activity diary. At the completion of the week the RT3 data will be downloaded to a portable computer and each participant will complete a 7-day recall questionnaire (7D-PAR) [71,72]. The 7D-PAR provides an estimate of the average total daily energy expenditure (TDEE) and physical activity energy expenditure (PAEE) for each participant.

All participants will be sent a reminder letter between the first and second period of monitoring; further contact will be made approximately 1 week prior to their scheduled date for re-monitoring at the 3-month point. Each participant will then repeat the activity monitoring procedure as per the baseline. At completion of week 12 each participant will be asked to complete the RMDQ, VAS and simple activity question and in addition an RT3 utility questionnaire developed for this study. This will assess any specific utility issues of PA measurement within this patient population.

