## Analyses

Multiple linear regression will be used to investigate the associations of the main predictor variable, change in RT3 VM counts/hour/week (ΔRT3) from baseline to 3 months, with the main outcome variable change in functional outcome (ΔRMDQ). The change score will be calculated by subtracting each participant's 3 month RMDQ score from their baseline RMDQ score. Unadjusted and adjusted analyses will be performed. Adjusted analyses will include the following variables, shown to be putatively associated with both PA and functional recovery in LBP: age, gender, occupation, baseline pain level (pain questionnaire), functional status (baseline RMDQ) and baseline measurements of depression, anxiety, emotional distress and fear avoidance (GHQ12 and FABQ). We plan to analyze each of the explanatory variables univariately initially to assess the relationship with the dependant variable (RMDQ change). We will include factors in the model which in univariate analyses have a *p*-value < 0.10. The significant explanatory variables contained in the separate models will then be combined and re-examined using further modeling. We plan to use multiple linear regression to assess which of the included explanatory variables and/or their interactions with PA change predict change in RMDQ. For those variables which remain in the final model, an examination of their significance (p < 0.05) will be undertaken to evaluate their contribution to the final model.

At 1 year the relationship between ΔRT3 and presence or absence of on-going low back pain (Y/N) from the modified Nordic LBP questionnaire will be investigated using logistic regression. At 1 year the relationship between the BPAQ change score from baseline (pre-LBP) to BPAQ score at 1 year (ΔBPAQ) with the outcome of on-going LBP (Y/N) will also be explored using logistic regression.

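### The primary 3-month regression relates two changes over the same interval, so it can show a concurrent association but not that activity predicts recovery; the one later-outcome ΔRT3 model does not close the gap

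*Protocol article*

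**What the plan says.** All references are to the protocol article.

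- **Predictor and outcome.** Analyses names the main predictor and main outcome as "change in RT3 VM counts/hour/week (ΔRT3) from baseline to 3 months, with the main outcome variable change in functional outcome (ΔRMDQ"). The outcome interval is fixed in the next sentence: "The change score will be calculated by subtracting each participant's 3 month RMDQ score from their baseline RMDQ score".
- **Timing.** Under Physical activity measurement, the second monitoring week takes place at 3 months, and "At completion of week 12 each participant will be asked to complete the RMDQ, VAS and simple activity question".
- **Covariates.** The adjusted model lists age, gender, occupation, and baseline pain, RMDQ, GHQ12 and FABQ. None is measured after baseline.
- **Claim.** Research objective 1 speaks of a predictive relationship. Hypothesis 1 says "Positive changes in PA levels of participants with acute LBP (from baseline to 3 months) are a positive predictor of recovery", with recovery defined by RMDQ change, at 3 months and at 1 year. The Discussion paragraph of the Abstract expects the results to "help to determine the strength of evidence supporting international guidelines that recommend restoration of normal activity in managing LBP".
- **1-year models.** Analyses plans two logistic regressions. The first is introduced as "At 1 year the relationship between ΔRT3 and presence or absence of on-going low back pain (Y/N"), with the outcome taken from the modified Nordic questionnaire. The second relates the "BPAQ change score from baseline (pre-LBP) to BPAQ score at 1 year" to the same outcome. RMDQ is also in the 1-year postal pack, but the Analyses section describes no model for it.

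**The concern.** ΔRT3 is not known until the second monitoring week is over, and ΔRMDQ is complete at that same point. Patients whose back pain settles can be expected to move more. A positive coefficient is therefore compatible with the hypothesis, with its reverse, or with a mixture. Baseline covariates cannot separate these, because the ambiguity arises within the 12 weeks.

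The wording matters because of the intended use. Evidence bearing on advice to restore activity needs, at the least, activity measured before the recovery it is said to predict. The 1-year ΔBPAQ model shares the problem at its end point: the second BPAQ score and the pain answer come back in the same postal pack.

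**Working it through.** **1. Time order of each planned model**

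| Model | Predictor known at | Outcome | Stated adjustment for 3-month RMDQ | Time-ordered? |
|---|---|---|---|---|
| ΔRMDQ on ΔRT3 | 3 months | RMDQ change, complete at 3 months | not applicable | No |
| 1-year pain (Y/N) on ΔRT3 | 3 months | Pain item at 1 year | None | Yes, but ΔRT3 may carry 3-month recovery |
| 1-year pain (Y/N) on ΔBPAQ | 1 year | Pain item at 1 year | None | No, concurrent at end point |

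**2. Size of the ambiguity in the primary model**

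Inputs from the article: n = 65 and two-sided alpha 0.05 (Sample size and statistical power). Assumption: activity has no effect on RMDQ, and recovery produces a correlation ρ between the two changes. The article gives no ρ, so a range is shown.

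Chance of p<0.05 by the Fisher z approximation: Φ(δ − 1.96) + Φ(−δ − 1.96), with δ = atanh(ρ) × √(n − 3) and √62 = 7.874.

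| ρ | atanh(ρ) | δ | Formula | Simulation |
|---|---|---|---|---|
| 0 | 0 | 0 | 5% | about 5% |
| 0.1 | 0.1003 | 0.790 | 12% | 11–14% |
| 0.2 | 0.2027 | 1.596 | 36% | 35–36% |
| 0.3 | 0.3095 | 2.437 | 68% | 68% |
| 0.4 | 0.4236 | 3.336 | 92% | 92% |
| 0.5 | 0.5493 | 4.325 | 99% | 99% |

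The simulation (two sets of 4,000 runs per ρ) fitted the planned regression adjusted for baseline RMDQ. Baseline was generated independently of change, so adjustment made no difference there. A second simulation (n=65, 2,000 runs) let current disability lower current activity, with assumed cross-sectional correlations of about −0.12, −0.24 and −0.34. The regression was significant in 28%, 78% and 98% of runs unadjusted, and in 19%, 61% and 91% adjusted for baseline RMDQ. Baseline adjustment reduces the excess but does not remove it.

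**3. Whether the planned 1-year ΔRT3 model removes it**

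Suppose the 1-year outcome depends only on recovery by 3 months, with assumed correlation s = 0.5 or 0.7. ΔRT3 then correlates with the 1-year outcome at ρ × s. At ρ = 0.3:

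- s = 0.5: ρs = 0.15, δ = 0.1511 × 7.874 = 1.190, chance 22%.
- s = 0.7: ρs = 0.21, δ = 0.2132 × 7.874 = 1.679, chance 39%.

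Simulation gave the same 22% and 39%. With 3-month recovery added to the model it returned to about 5%. These figures use a continuous outcome. In the second simulation, the yes/no outcome as planned gave 6%, 12% and 19%, and 4–5% once baseline and 3-month RMDQ were added. The unadjusted 1-year model is therefore less affected than the primary model, but not free of the problem.

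**The case against.** **An ordered model is planned.** A reader might infer that the plan contains no temporally ordered model. That is wrong: the logistic regression of 1-year pain on 0–3 month ΔRT3 puts the predictor first, and Hypothesis 1 explicitly extends to 1 year. Hypothesis 3 also relates earlier activity status to recovery over 1 year. What stands is narrower: the ordered ΔRT3 model has a different outcome from the recovery defined in Hypothesis 1, and it states no adjustment for recovery already achieved.

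**The language is often cautious.** Analyses speaks of associations for the main model and of exploring the ΔBPAQ relationship. The design is declared observational, no hypothesis states cause, and predictor is an ordinary regression term. This is fair, and it confines the wording point to Research objective 1, Hypothesis 1 and the guideline sentence in the Abstract.

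**Reverse causation is not shown.** A reader might infer that a positive result is to be expected whatever activity does. The article does not support that. Its Background cites an accelerometer cohort in which activity change did not differ between recovered and non-recovered patients. It also cites a questionnaire cohort in which developing chronic pain did not affect energy expenditure, and says that cross-sectional work gives little evidence of a direct link. If the reverse path is nil, so is the inflation.

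**The size depends on the model.** When activity was made to follow true disability and RMDQ carried measurement error (SD 2–3, assumed), the planned adjusted model fell from 95% to 58–78% under the strongest reverse path tried. A model using baseline RT3 to predict 3-month change rose from 5% to 8–12%, and the 1-year RMDQ model adjusted for 3-month RMDQ stayed near 5–6%. This rules out quoting one rate as the answer, and it is a reason not to lean on the baseline-RT3 model.

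**The remedy asks a different question.** Conditioning on 3-month RMDQ removes any benefit of activity realised by then. That is true, and it is the price of time order.

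**Conclusion.** The concern holds in this form. The primary model is concurrent and cannot distinguish activity predicting recovery from recovery raising activity, yet Research objective 1 and Hypothesis 1 call the relation predictive and the Abstract ties it to activity guidelines. The one ordered ΔRT3 model does not repair this, because of its outcome and because no adjustment for 3-month RMDQ is stated.

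The size is conditional. At n=65, with no effect of activity, the primary regression is significant in 5% of studies if recovery does not move activity, about 35% at an assumed change–change correlation of 0.2, and 68% at 0.3. The time-order conclusion follows from the article's own definitions and does not depend on those figures. The calculation and data collection are not invalid; what fails is the predictive reading of the 3-month result.

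**What to change.** 1. In Research objective 1 and Hypothesis 1, describe the 3-month ΔRT3–ΔRMDQ result as a concurrent association. Interpret ΔBPAQ against 1-year pain in the same way.
2. Add a regression of 1-year RMDQ on ΔRT3 (baseline to 3 months), adjusted for baseline and 3-month RMDQ.
3. Add 3-month RMDQ to the planned logistic regression of 1-year pain on ΔRT3.
4. Rest any claim of prediction on the models in 2 and 3.
5. Optionally, report baseline RT3 predicting 3-month RMDQ given baseline RMDQ as supporting evidence. It concerns activity level, not change.

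Cost: rewording, one further regression and one added covariate. RT3 at both occasions and RMDQ at baseline, 3 months and 1 year are already collected. The downside is real: the 1-year models have lower power, fall at the last time point of a study that allows for 40–50% loss, and exclude any benefit already realised by 3 months. They establish time order, not cause.

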### Study design

A cohort study recruiting patients by public advertising: this will include local newspapers, public notice boards, posters, mail-outs to local physiotherapy clinics in the urban and sub-urban environment of a city in New Zealand, as well as email notification of university staff and students at the University of Otago, Dunedin. All participants who are interested in the study will be encouraged to contact the principal investigator (PI) via telephone or e-mail. Recruitment will take place over a one year period. Assessment and monitoring of each participant's activity levels will take place after attending their physiotherapist for acute LBP treatment with follow-up assessments and activity measurements at 3 and 12 months.

The study protocol has been approved by the Lower South Regional Ethics Committee (LRS/07/11/043) and the Ngâi Tahu Research Committee following Maöri consultation.

### Inclusion and exclusion criteria

To be eligible to take part in the study, participants must fulfil the following criteria:

1) Have an episode of LBP of 6 weeks or less, proceeded by at least 3 months of relative freedom from symptoms. These inclusion criteria will effectively exclude the chronic LBP population (defined as symptoms exceeding 3 months) [55].

2) Be between the ages of 18 and 65 years (working age population).

3) Be English speaking and able to provide informed consent to PA monitoring and follow up for 12 weeks.

4) Have no other pre-existing conditions which limit their mobility of PA levels.

5) Be receiving physiotherapy treatment for this current episode of acute LBP. This threshold was chosen to make results generalizable to this specific patient population.

6) Have a minimal score of 4 on the RMDQ. This score will allow for the detection of the smallest clinically important change [55].

The following exclusion criteria will be investigated at an initial screening interview by the PI prior to recruitment:

1) Serious or systemic spinal pathologies including persistent or progressive neurological deficit, intractable pain, spinal surgery, or inflammatory disorders as assessed by their health practitioner or by screening questions from the co-investigator.

2) Any history of current or past medical problems (other than LBP) which prevent participants from undertaking usual day-to-day activities.

